#### Features associated with foot OA phenotypes

Linking data collected at the clinical assessment with that from the baseline health survey questionnaire, the occurrence of radiographic OA will be related cross-sectionally to foot pain and disability, foot deformities, soft-tissue problems, footwear characteristics and pain/OA at other sites, using odds ratios and associated 95% confidence intervals adjusted for age, gender and BMI. The effect of missing primary outcome data will be investigated using multiple imputation methods.

#### Outcome of foot OA at 3 years

Linking baseline date to 18-month and three-year follow-up questionnaires, we will then be able to determine prospectively the factors that are related to clinical deterioration using risk ratios and associated 95% confidence intervals, for example, radiographic OA, footwear characteristics, pain/OA at other sites, psychosocial factors.

#### The presentation and diagnosis of OA in primary care

Participants with a recorded consultation for joint-related problems will be classified into those receiving an OA diagnosis recorded by their GP and those receiving a non-specific symptom code (e.g. arthralgia). The proportion of participants who (a) consult and (b) are diagnosed with OA will be described using simple descriptive statistics. Logistic regression will be used to identify which features, including OA phenotype, are strongly associated with consultation and foot OA-diagnosis. The effect of missing primary outcome data will be investigated using multiple imputation methods.

#### Describing self-care and primary care

Annual consultation rates and cumulative consultation probabilities will be calculated over the three-year period. Using logistic regression and survival analysis techniques, we will investigate further how different phenotypes relate to subsequent patterns of primary care consultation (for joint pain, other morbidities, and specifically for OA) and referral to secondary care. Self-care reported by participants in the surveys at each 18 month time-point will be described.

#### Modelling the outcomes of care

We will model the effects of care on impairment, activity limitation and participation restriction. We aim to use propensity scores (ie the propensity or likelihood of a person to seek healthcare given their characteristics) and random effects repeated measures multilevel models in order to take into account the effects of both observed and unobserved covariates on outcome at each follow-up time point. Using consultations and secondary care referrals from medical record review, together with socio-demographic, clinical, general health and phenotype characteristics, we will apply these methods to a series of analyses in which the separate effects of each of the components of consultation on subsequent outcomes at each follow-up time point will be modelled.

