**Figure 1 F1:**
[figure not shown]
**Flowchart of study procedures**.

Phase 1: Baseline postal Health Survey questionnaire

Phase 2: Baseline Clinical Assessment Study of the Foot (CASF)

Phase 3: Review of general practice medical records

Phase 4: Follow-up mailed survey at 18 months (Phase 2 participants only)

Phase 5: Follow-up mailed survey at 3 years (Phase 1 and Phase 2 participants)

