### Phase 4: Follow-up mailed survey at 18 months (Phase 2 respondents only)

Follow-up surveys will be mailed to all Phase 2 participants 18 months after their baseline clinical assessment. The focus of follow-up will be clinical (severity of pain and functional limitation) change and possible determinants of this. The content of this survey is provided in Table 3. Non-responders to the questionnaire will be sent a reminder postcard after two weeks. Those who do not respond to the reminder postcard will be sent a repeat questionnaire and Participant Information Sheet with a further covering letter four weeks after the initial mailing. Primary outcome data will be sought from non-respondents by telephone interview or shortened postal questionnaire. We plan to trace participants who have moved practice during the follow-up period using the NHS tracing service.

**Table 3 T3:** Content of 18-month postal follow-up Health Survey questionnaire (Phase 2 participants only)

Concept	Measurement method	Detail
Foot pain characteristics	Change in foot pain over past 18 months	Completely recovered, much better, better, no change, worse, much worse
	Since your assessment 18 months ago, have you ever injured your foot badly enough to see a doctor about it?	No/right only/left only/both
	Foot pain, aching, stiffness in last month [39]	No days, few days, some days, most days, all days
	Foot pain intensity in past month [40]	0-10 NRS with verbal anchors (no pain, pain as bad as could be)
Foot pain chronicity	Chronic Pain Grade [59]	6 questions (0-10 NRS) and 1 question (4 response options) giving grade I-IV
Complaint-specific functioning	Manchester Foot Pain and Disability Index [41]	19-items across four constructs: pain, function, appearance, work/leisure
	Symptom satisfaction [64]	5-point Likert scale (Very dissatisfied to Very satisfied)
Healthcare use	Use of services/treatments for foot pain in past 18 months	GP, physiotherapist, hospital specialist, acupuncture, podiatrist, chiropodist, drugs on prescription, foot injection, foot surgery, osteopath/chiropractor, other (specify)
	Medication use in last month	For foot pain, for other pain
Coping strategies for foot pain	Single-item coping strategies questionnaire [42]	0-6 NRS with verbal anchors (never do that, always do that)
Perceived general health	MOS SF 12 [33]	Physical and mental component summary scores
Physical function	MOS SF 36 [32]	Physical functioning sub-scale

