**Section A: General health**		
Perceived general health	MOS SF 12 [33]	Physical and mental component summary scores
Physical function	MOS SF 36 [32]	Physical functioning sub-scale
Anxiety and depression	Hospital anxiety and depression scale [34]	Anxiety and depression sub-scales
Participation	Keele Assessment of Participation (KAP) [35,73]	5-items assessing person-perceived, performance-based participation
Physical activity	Short-Form International Physical Activity Questionnaire (IPAQ) [36]	Frequency and duration of 4 activities performed during previous 7 days
		

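### Participation restriction is to be modelled at each follow-up, but the only listed participation measure (KAP) is not in the 18-month questionnaire

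*Protocol article*

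**What the plan says.** The section Modelling the outcomes of care names three outcome domains: "We will model the effects of care on impairment, activity limitation and participation restriction". The method is propensity scores together with "random effects repeated measures multilevel models in order to take into account the effects of both observed and unobserved covariates on outcome at each follow-up". The section closes by promising that "the separate effects of each of the components of consultation on subsequent outcomes at each follow-up time point will be modelled".

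The list of phases under Study design gives two follow-ups: "Phase 4: Follow-up mailed survey at 18 months (Phase 2 participants only)" and "Phase 5: Follow-up mailed survey at 3 years (Phase 1 and Phase 2 participants)".

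The questionnaire contents are set out row by row in Tables 1, 3 and 4. Tables 1 and 4 each have a row for the concept of participation, filled by "Keele Assessment of Participation (KAP)". Table 3, titled "Content of 18-month postal follow-up Health Survey questionnaire (Phase 2 participants only)", has no such row.

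**The concern.** The analysis section promises an effect at every follow-up for each of three domains, but the data collection supports this for participation at only one of the two follow-ups. An analysis plan that is not shown cannot repair this, because no analysis can use answers that the questionnaire did not ask for. Once the 18-month forms have gone out, the value is lost for those who received them.

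Participation is also more than a passing word. The Background gives the lack of evidence on the long-term effect of primary care on impairment, activities and participation as part of the reason for the study. Someone who reads the analysis section as a commitment will expect an 18-month participation result that cannot be delivered from KAP.

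**Working it through.** No arithmetic in the plan bears on this point. The sample-size calculation concerns poor functional outcome at 3 years and does not involve KAP. The check is a comparison of the questionnaire tables with the analysis section.

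**Step 1. Follow-up points.** There are two: 18 months (Phase 2 only) and 3 years (Phases 1 and 2).

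**Step 2. What is collected at each wave** (Tables 1, 3 and 4):

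| Measure | Baseline | 18 months | 3 years | Follow-up values |
|---|---|---|---|---|
| Foot pain intensity | yes | yes | yes | 2 of 2 |
| Manchester Foot Pain and Disability Index | yes | yes | yes | 2 of 2 |
| SF-12 | yes | yes | yes | 2 of 2 |
| SF-36 physical functioning | yes | yes | yes | 2 of 2 |
| Hospital anxiety and depression scale | yes | yes | yes | 2 of 2 |
| KAP | yes | **no** | yes | **1 of 2** |

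**Step 3. Is the gap only a matter of a condensed article?** Table 3 is presented as the content of the 18-month survey and goes down to date of birth and employment status. A whole instrument is unlikely to have been dropped for brevity when such items are kept.

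**Step 4. Could another 18-month item be the participation outcome?** The candidates are the work/leisure part of the Manchester index, SF-12, Chronic Pain Grade and employment status. The tables file these under complaint-specific functioning, perceived general health, foot pain chronicity and socioeconomic characteristics. None is designated as participation.

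**Step 5. What follows for the model, if KAP is the outcome?**
- The effect at 18 months has no outcome data and cannot be estimated.
- With one post-baseline value per person, a person-level random effect cannot be separated from residual error. It becomes separable only if baseline KAP is treated as a response too, which gives two occasions.
- The 3-year effect adjusted for baseline KAP can still be estimated.
- Consultations and referrals come from medical records covering the three years after clinic attendance (Phase 3). Care in months 0-18 and in months 18-36 can therefore be entered as separate exposures for 3-year KAP. What is lost is the intermediate outcome value, not the dating of care.

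**Step 6. Who is affected?** All Phase 2 participants are affected. The recruitment target is 506, and the plan allows for a drop-out of 80 by three years (506 − 80 = 426). Hence 506 is an upper bound for the number who would have given an 18-month value.

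**The case against.** The strongest reply is that the contradiction depends on a mapping the document never makes. The analysis section names no instrument for any of its three domains, and assigning instruments to domains is detail that an article may leave to a fuller plan. This stands as a condition on the finding. It does not remove it, because KAP is the only instrument labelled as participation anywhere in the tables. If a different measure is intended, the plan needs to say so.

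Second, the short 18-month survey looks deliberate. The Phase 4 text gives its focus as change in pain severity and functional limitation, and the physical activity questionnaire and the co-morbidity list are also left out and return at 3 years. That explains the omission well, but it also confirms that the analysis section promises more than Phase 4 collects.

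Third, the wording about each follow-up could mean each point at which the given outcome is collected. Phase 1-only participants have just one follow-up in any case, and the section speaks of a series of analyses and of methods it aims to use. This reading is possible, and one sentence would settle it.

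The objection is right about the consequences. A reader might infer that care in the two 18-month intervals can no longer be told apart, or that participation has no longitudinal analysis left. The documents do not support either inference: the records date the care, and change in KAP from baseline to 3 years is available. A reader might also want to express the gap as a loss of precision. The document gives no correlation between waves to base that on, and an average over the two follow-ups is not what the section plans to estimate.

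**Conclusion.** The mismatch is real but limited. If KAP is the participation outcome, the planned effect of care on participation cannot be estimated at 18 months, and the repeated-measures model for that domain has one post-baseline value instead of two. One of three outcome domains is affected, at one of two follow-ups, in all Phase 2 participants.

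The conclusion rests on two things: that KAP stands for participation, which follows from its being the only instrument so labelled, and that Table 3 is complete, as it is presented.

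Two parts of the study are untouched. The primary comparison concerns functional outcome at 3 years. Aim (vi) concerns severe foot pain, and pain intensity and Chronic Pain Grade are in both follow-up surveys. The point therefore merits a correction before the 18-month mailing but does not threaten the main results.

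**What to change.** Preferred: add the five-item KAP to the 18-month questionnaire (Table 3) before the first of these forms is mailed. The cost is five more questions and a minor document update, with slight extra burden on respondents in a survey meant to be short.

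Otherwise: amend Modelling the outcomes of care so that participation restriction is modelled at 3 years only, adjusted for baseline KAP, with care from the medical records split into 0-18 and 18-36 months where that is of interest. This costs a sentence or two, and the 18-month participation effect is given up openly.

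In either case, name KAP (or whichever measure is intended) as the participation outcome in that section.

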In addition to the questions of what phenotypes present to primary care and how they are managed, a crucially important issue is what effect primary care management has on outcome. Non-consultation for peripheral joint problems is common. Approximately 80% of those with musculoskeletal foot problems do not appear to consult their GP over prolonged periods of time (three years) [28]. Part of this is likely be related to the belief, pervasive among both the public and practitioners, that "nothing can be done". Furthermore, despite randomised controlled trial evidence about the short-term efficacy of primary care treatment for some peripheral joint problems [29], there are few investigations of the long-term effect of primary care consultation or OA management on impairment, activities or participation.

In summary, there is a paucity of research evidence concerning the radiographic phenotypes of foot OA and their impact on symptoms, clinical features, activity limitation and participation restriction. Important questions concerning how clinical phenotypes relate to the diagnosis of OA in primary care, and how the outcome from foot pain and OA is influenced by primary care consultation have been under-researched in relation to the foot but also at other joint sites. This prospective, observational, cohort study will combine unselected population sampling of older adults, self-reported survey data, comprehensive clinical and radiographic assessment, and linkage to computerised primary care records, to address these issues over a three-year period. It is designed to complement earlier studies of knee pain and OA [30] and hand pain, problems and OA [31] and permit combining of data across all three cohorts as well as direct comparison between them.

The aims of the study are to:

(i) Describe the frequency and pattern of co-occurrence of radiographic features of symptomatic OA in the following foot joints: the 1^st ^MTPJ, the 1^st ^and 2^nd ^CMJs, the NCJ and the TNJ.

(ii) Relate the occurrence of radiographic OA, described above, cross-sectionally to foot pain and disability, foot deformities, and soft tissue problems on physical examination. The associations between foot OA, foot pain, disability and footwear will also be examined.

(iii) Determine prospectively the factors that predict clinical deterioration, for example, radiographic OA, footwear characteristics, pain/OA at other sites, and psychosocial factors.

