(iv) Identify which foot pain phenotypes present to primary care and are diagnosed in this setting.

(v) Describe the patterns of self-care and primary health care use for foot OA.

(vi) Model the effects of care on the outcome of severe foot pain.

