**Section C: Foot pain**		
Foot pain characteristics	Side of pain	Both, right, left
	Duration in past 12 months	< 7 days, 1-4 weeks, 1-3 months, 3+ months
	Foot injury: Have you ever injured your foot badly enough to see a doctor about it?	No, right foot only, left foot only, both feet
	Foot pain, aching, stiffness in last month [39]	No days, few days, some days, most days, all days
	Location: self-completed foot manikin [14]	In the past month, have you had any ache or pain that has lasted for one day or longer in your feet? If yes, shade pain location on foot manikin
	Foot pain intensity in last month [40]	0-10 NRS with verbal anchors (no pain, pain as bad as can be)
Complaint-specific functioning	Manchester Foot Pain and Disability Index [41]	19-items across four constructs: pain, function, appearance, work/leisure
Coping strategies for foot pain	Foot-related fatigue: single item Single-item coping strategies questionnaire [42]	None of the time, on some days, on most/every day(s) 0-6 NRS with verbal anchors (never do that, always do that)
Healthcare use	Medication use in last month	For foot pain, for other pain
	Consultation in last 12 months for foot pain	General practitioner, physiotherapist, podiatrist, chiropodist (NHS and private)

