**Self-complete questionnaire**		
***Section A: Foot Pain***		
Foot pain chronicity	Chronic Pain Grade [59]	6 questions (0-10 NRS) and 1 question (4 response options) giving grade I-IV
Complaint-specific functioning	Symptom satisfaction [64]	5-point Likert scale (Very dissatisfied to Very satisfied)

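### The effect-of-care analysis is said to account for unobserved covariates, but propensity scores and random effects do not control unmeasured confounding

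*Protocol article*

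**What the plan says.** Aim (vi), at the end of the Background, is causal in form: "Model the effects of care on the outcome of severe foot pain". The method is in the Statistical analysis section under Modelling the outcomes of care: "We aim to use propensity scores (ie the propensity or likelihood of a person to seek healthcare given their characteristics"), combined with multilevel repeated-measures models with random effects. The stated purpose of the combination is "in order to take into account the effects of both observed and unobserved covariates on outcome at each follow-up time point". Consultations and referrals from the medical records supply the exposure, and they are used "together with socio-demographic, clinical, general health and phenotype characteristics".

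Care is self-selected. The Background reports: "Approximately 80% of those with musculoskeletal foot problems do not appear to consult their GP over prolonged periods of time (three years").

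Baseline severity is well measured. The Health Survey (Table 1) has a 0-10 pain intensity rating, the Manchester Foot Pain and Disability Index, SF-12, SF-36 physical function and the Hospital anxiety and depression scale. The clinic questionnaire (Table 2) adds the Chronic Pain Grade: "6 questions (0-10 NRS) and 1 question (4 response options) giving grade I-IV". Severity is then measured only twice more. At 18 months, "Follow-up surveys will be mailed to all Phase 2 participants 18 months after their baseline clinical assessment"; the last survey is at three years.

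**The concern.** The sentence credits the two methods with a property that neither has when the target is an effect of care. The propensity score is defined from a person's recorded characteristics, so it can balance only those. The random effect does represent unobserved differences between people in outcome, but on the assumption that those differences are unrelated to who receives care. Confounding by unmeasured severity is a failure of exactly that assumption. The article does not state the assumption, and it names no instrument, within-person contrast or bias analysis that could support the claim.

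At stake is what aim (vi) can conclude. If people consult when their feet are worse in ways the surveys miss, care will tend to look useless or harmful. The plan's wording would invite readers to treat that result as already corrected for unobserved differences.

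**Working it through.** **The plan's own figures.** This section gives none. The only design figures concern radiographic OA against none. They reproduce and are unaffected. With p1 = 0.20 and p2 = 0.20 × 1.62 = 0.324, two-sided 5%, 80% power and equal groups (two-sidedness and equal groups are assumed), the two-proportion formula gives 197 per group. With continuity correction it gives 213 per group, and 2 × 213 = 426. Adding 80 for drop-out gives 506.

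**Step 1: the algebra.** Write the outcome of person i at follow-up t as

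y_it = β·care_it + γ·PS_it + b_i + e_it,

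with b_i the random person effect. The estimate of β is free of confounding only if, given the propensity score PS, care_it is independent of both b_i and e_it. Stable unmeasured severity that prompts consultation breaks the first condition. A flare between surveys that prompts consultation breaks the second. Estimating b_i repairs neither.

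**Step 2: illustrative simulation.** All inputs here are assumptions, not figures from the documents.
- 20,000 people, two follow-ups, true effect of care zero.
- Log-odds of care = -0.8 + 0.5 × measured severity + 0.5 × unmeasured severity, the last term set to zero in the first row below.
- Outcome = 0.5 × measured severity + 0.5 × a stable person effect + noise with SD 0.7. In the second row the stable person effect is the unmeasured severity. In the third row a separate time-varying severity also enters with coefficient 0.5.
- Outcome variance is 0.25 + 0.25 + 0.49 = 0.99, so coefficients are close to SD units. In the third row it is 0.99 + 0.25 = 1.24 (SD 1.11).
- Model: propensity score as a covariate plus a random intercept.

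| Confounding | Crude | Propensity score + random intercept | Baseline outcome added | Within-person (Mundlak) |
|---|---|---|---|---|
| All measured | 0.25 | 0.01 | 0.01 | 0.02 |
| Stable, partly unmeasured | 0.45 | 0.16 | 0.12 | 0.00 |
| Time-varying, partly unmeasured | 0.44 | 0.22 | 0.22 | 0.23 |

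The planned model removes measured confounding and leaves unmeasured confounding. A within-person contrast removes only the stable part.

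**Step 3: dependence on how well severity is measured.** The setting is 426 people, two 18-month intervals, about 19% receiving care in each, and unobserved severity raising the odds of care 2.2-fold per SD. Only the reliability of the adjusted severity score is varied (100 datasets per setting, true effect zero):

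| Reliability | Spurious coefficient | Rejections at 5% |
|---|---|---|
| 0.61 | 0.198 | 65% |
| 0.85 | 0.102 | 28% |
| 0.95 | 0.042 | 11% |

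The bias shrinks steeply as measurement improves. The 19% is also generous: 1 - 0.81² = 34% ever receiving care if the intervals were independent, against about 20% consulting over three years on the Background's figure.

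**Step 4: whether a within-person estimate is a safe replacement.** Let care in the second interval also depend on the 18-month outcome, with the true effect still zero. The within-person estimate then becomes -0.126 (21% rejections) at an odds ratio of 1.5 and -0.239 (64%) at 2.2, a spurious benefit. At 2.2 the planned model was less biased, at 0.099 (26%). A separately built simulation gave the same pattern: -0.16 at a log-odds coefficient of 0.4 and -0.30 at 0.8, worse still when an interval-specific propensity score was added to the within-person model.

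**The case against.** Several points count for the plan.

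- **Severity is measured with several instruments, and clinical characteristics enter the models.** This stands. A reader might infer that confounding by severity will appear as an effect of care. The documents do not support that: confounding by measured severity is adjustable (first row in Step 2), and they give no size for the unmeasured remainder. A figure such as 65% false rejections reflects one unfavourable set of assumptions.
- **The sentence speaks of covariate effects on outcome, and random effects do model unobserved heterogeneity in outcome.** As a description of the model this is fair. But the sentence justifies an effect-of-care analysis, where readers will take it as control of confounding.
- **It is worded as an aim, for the last of six objectives.** This softens the commitment to the methods, not the property claimed for them. The primary comparison is untouched.
- **Details of the score belong in a fuller document.** This also stands. A reader might infer that one propensity is estimated at baseline and applied to all later care. The text does not say so, and it refers to outcomes at each follow-up, which is compatible with updating. Timing of the score is therefore not counted as an error here. It appears under the fix only because the corrected claim depends on it.

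**Conclusion.** The claim to account for unobserved covariates should not stand for an analysis of the effects of care. This rests on what the two methods assume, not on any simulation input. The consequence is a risk: residual confounding by unmeasured severity may bias the aim (vi) estimates, most plausibly making care look worse than it is. Its size cannot be derived from the documents. Under the assumptions shown it ranged from about 0.01 when all confounding is measured to about 0.2 on the outcome scale when a substantial part is not.

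A reader might also infer that a within-person model should become the reported estimate. That is not supported. It fails under time-varying unmeasured severity, and it can manufacture a benefit if later care responds to 18-month status, which is plausible in this setting.

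**What to change.** 1. Limit the statement to measured covariates. Say that the random effects model heterogeneity in outcome on the assumption that it is independent of receiving care, and that they do not remove unmeasured confounding.
2. For care after the 18-month survey, adjust for status at that survey as well as at baseline. A separate model for the second interval is cleaner, because the 18-month score is itself the response for the first. This is possible only where the outcome is collected at 18 months: pain intensity, the Manchester index, Chronic Pain Grade and SF-36 function are in Table 3, but the participation measure (KAP) is only in Tables 1 and 4. It applies to Phase 2 participants only, since others receive no 18-month survey.
3. Report a quantitative bias analysis with each effect-of-care estimate, such as an E-value (for a risk ratio RR above 1, RR + √(RR × (RR - 1))) for the estimate and for its confidence limit nearer the null.
4. If a within-between (Mundlak) estimate is added, label it a sensitivity analysis. State its assumptions: no feedback from earlier outcome to later care, and no time-varying unmeasured confounding.

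The cost is modest extra analysis and a more cautious conclusion for aim (vi). No further data collection is needed and no sample-size figure changes.
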